## 3. Statistics Analyses

IBM SPSS Version 25 (Armonk, New York, USA) will be used to analyze the data. Both completer analyses and intention-to-treat analyses (using the method of last observation carried forward) will be carried out. Descriptive characteristics of the sample will be calculated as obtained counts (*n*) and simple proportions (%), with missing items reported as missing.

For study one, the measurements at three different time points will be compared using the analyses of variance (ANOVA) for continuous variables and the chi-square test for categorical variables.

In addition, in study two, the researchers will employ linear regression analyses to examine the predictors of PG-13, DASS-21, PCL-5 and PTGI at each time point, while controlling for gender, age, education level, marital status, and religious beliefs. The cross-lagged model will be used to further clarify the direction of the relationship between the predictors and outcome variables. A *p*-value < 0.05 (2-tailed) will be taken to indicate statistical significance.

For study three, Chi-square tests and ANOVAs will be conducted on baseline scores to rule out significant differences between groups on demographic or loss-related or outcome variables before treatment. The treatment effects on the primary outcome variables will be examined with a 2 (groups) × 3 (time points) multivariate analysis of variance (MANOVA), with three time points (baseline, post-counseling, and three months follow-up) as the repeated measures. The outcomes of treatments will be further investigated separately with the analyses of covariance (ANCOVA), using baseline scores of the outcome variables as covariates.

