### 2.3. Study 3: Grief Counseling for Bereaved Chinese during COVID-19

Based on the above grief therapy description, combined with the results of study two, the researchers will develop an online grief counseling plan that is more suitable for Chinese culture. The counseling is expected to include 8–10 sessions (one hour per session). The themes of each of the sessions are: (1) understanding and accepting grief reactions; (2) managing painful emotions; (3) learning to care for yourself; (4) increasing contact with others; (5) coping with difficult days; and (6) adapting to a new life.

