#### 2.3.2. Procedure and Measures

The researchers aim to conduct a single-blinded randomized controlled trial (RCT) evaluating the effectiveness of grief counseling versus a waitlist control group in reducing prolonged grief symptoms, post-traumatic symptoms, depression levels, and suicidal intentions in bereaved Chinese individuals in relation to COVID-19.

After finishing the baseline questionnaires and signing the informed consent, 160 bereaved participants will be randomly assigned to the grief counseling group or the waitlist group.

The sample size is calculated based on the expected difference on the primary outcome variable (grief symptoms of the bereaved) between the different groups. According to previous RCTs on bereaved individuals [43], we expect a medium Cohen effect size of 0.5 in the intervention group. The sample size calculation is based on the conventional significance (α) and power (1−β) levels of 0.05 and 0.80, respectively, and an expected dropout percentage of 20%. The result shows that we will need almost 80 participants for each group, therefore, we have determined the total sample size to be 160 in this study.

The measures in study three are the same as study three. Assessments will be conducted at three time points: before randomization (baseline, T0), at post-counseling (T1), and three months after the post-counseling (T2).

Table 2 shows which measures will be assessed at each time point. And Figure 1 shows the research process.

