## 5. Ethics, Consent and Permissions

This research will follow the latest version of the Declaration of Helsinki. The study protocol was approved by the Institutional Ethics Committee of Beijing Normal University and the Chinese clinical trial registry has approved the study (Register ID: ChiCTR2000038255). Informed consent to participate in the study will be obtained from all participants. Participants will be informed that they can withdraw at any time from the study without consequences.

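### The RCT plans both a completer analysis and an intention-to-treat analysis without saying which decides; the completer set is undefined, chosen after randomisation, and can be biased in either direction

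*Protocol article*

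**What the plan says.** Section 3 (Statistics Analyses) opens with a paragraph common to all three studies, which states: "Both completer analyses and intention-to-treat analyses (using the method of last observation carried forward) will be carried out". Intention-to-treat has meaning only for the randomised Study 3, so this is where the sentence has force. It neither ranks the two analyses nor defines a completer. The Study 3 paragraph of the same section plans a 2 × 3 MANOVA and then ANCOVA on baseline, without saying which analysis set either uses.

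Section 2.3.2 describes the trial as "evaluating the effectiveness of grief counseling versus a waitlist control group". Section 2.3 says of the intervention: "The counseling is expected to include 8–10 sessions (one hour per session"). During the comparison only the counseling arm has sessions to attend. Section 2.3.2 and Table 2 schedule assessments at baseline, post-counseling (T1) and three months later (T2). They set no condition on attendance, and do not say whether someone who stops counseling is still asked for T1 and T2 scores. Section 5 tells all participants that "they can withdraw at any time from the study without consequences".

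**The concern.** Randomisation protects a comparison only if people are analysed in the groups to which they were assigned. A completer set is selected by something that happens afterwards. If those who leave the counseling arm are doing worse than those who stay, and the waitlist is not thinned in the same way, the remaining counseled participants look better even when counseling does nothing. If people leave because they have recovered, the distortion runs against counseling.

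With two analyses planned and neither named as decisive, a disagreement between them has no rule to settle it. At stake is whether the trial's effectiveness conclusion rests on the randomised comparison.

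**Working it through.** **The plan's own figure.** Section 2.3.2 gives d = 0.5 ("we expect a medium Cohen effect size of 0.5 in the intervention group"), the "conventional significance (α) and power (1−β) levels of 0.05 and 0.80, respectively", 20% dropout not split by arm, and almost 80 per group. The two-sided level is stated in the Study 2 paragraph of section 3 and is assumed to apply here.

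- Normal formula: n = 2(1.96 + 0.842)²/0.5² = 62.8, so 63 per arm; 63/0.8 = 78.75, so 79.
- t-test version: 64 per arm; 64/0.8 = 80.

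The 80 per group is reproduced. The sample size is correct and is not at issue.

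**Illustration under no true effect.** Assumptions not in the article: correlation 0.5 between baseline and T1, no time trend, and correlation c between stopping and a worse course after baseline. There are 80 per arm, analysed by ANCOVA on baseline at two-sided 0.05.

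*By formula, 20% removed from the counseling arm and none from the waitlist.* Removing the worst fraction f of a standard normal variable correlated c with outcome shifts the mean of the rest by c·φ(z)/(1 − f). For f = 0.2, z = 0.842 and φ(z) = 0.280, so the shift is c × 0.280/0.8 = 0.35c.

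- c = 0.3: 0.105 residual SD. The residual SD after baseline adjustment is √(1 − 0.5²) = 0.866, so the bias is 0.105 × 0.866 = 0.09 SD.
- c = 0.5: 0.175 residual SD, so 0.175 × 0.866 = 0.15 SD.

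With 64 and 80 analysed, the standard error is √(1/64 + 1/80) = 0.168 residual SD. The shifts are then 0.63 and 1.04 standard errors, and the two-sided rejection rates are about 10% and 18%.

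*By simulation, 3,000 trials per scenario:*

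| Removed (counseling / waitlist) | c | Completer bias (SD) | Completer false positives | LOCF bias (SD) | LOCF false positives |
|---|---|---|---|---|---|
| 20% / 0% | 0 | 0.00 | 5.1% | 0.00 | 5.2% |
| 20% / 0% | 0.3 | 0.09 | 10.9% | 0.08 | 9.8% |
| 20% / 0% | 0.5 | 0.14 | 16.1% | 0.11 | 13.7% |
| 30% / 10% | 0.5 | 0.13 | 14.7% | 0.08 | 10.0% |
| 20% / 20% | 0.5 | 0.00 | 5.7% | 0.00 | 5.2% |

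Bias is shown as false benefit to counseling. Formula and simulation differ by at most about two percentage points in false positives. A repeat with 20,000 trials of the 20% / 0% completer scenarios gave 9.5% and 18.1%, so the formula values are the steadier ones. If stopping is tied to a better course, the sign reverses.

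*Everyone followed and analysed as randomised.* In all simulated scenarios (c from 0 to 0.7) the bias was within 0.006 SD of zero and false positives were 4.1% to 5.2%.

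Two things follow. The completer bias depends on dropout differing between the arms. And LOCF intention-to-treat is biased almost as much in the one-sided case, so ranking it first without collecting stoppers' scores would gain little.

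**The case against.** The strongest reply is that a completer is never defined. The contrast with last observation carried forward, in a paragraph that also covers a survey with no treatment, suggests it may mean someone with all assessments. Waitlist participants can then be non-completers too, and equal dropout by the same mechanism gives about zero bias (false positives 4.7% to 6.6% across the correlations tried). This stands. A reader might infer that only the counseling arm can be filtered, but the text does not establish it.

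A reader might also infer from section 5 that stopping counseling and leaving the assessments are one event. That sentence is a general consent statement for all participants. Section 1.5 separates receiving the service from giving data, and the assessment schedule is not tied to attendance. The article does not merge the two events; it only leaves open what happens after someone stops counseling.

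The 20% in section 2.3.2 is not split by arm, and the 80 per group is reproduced by inflating both arms. Placing it all in the counseling arm is therefore an assumption. A larger figure, about 0.25 SD and 29% false positives, can be obtained unadjusted with 30% outcome-related dropout in counseling and 10% random dropout on the waitlist. It needs different mechanisms in the two arms, which nothing in the article supports.

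Finally, ranking analysis sets is often left to a full protocol or analysis plan, and the article nowhere permits an effectiveness claim from completers alone. That limits the weight of the point. It does not remove it: the article itself commits to two analysis sets for its one randomised comparison and leaves open which one answers the question.

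**Conclusion.** The point holds in limited form. The article commits the RCT to a completer and an LOCF intention-to-treat analysis with neither deciding. The completer set is not the randomised comparison on either reading of the term. Under no true effect, with 20% outcome-related dropout in the counseling arm only and correlation 0.3 to 0.5, the false benefit is about 0.09 to 0.14 SD in simulation (0.09 to 0.15 by formula). Against the planned 0.5 SD this is roughly a fifth to three tenths. False positives are 11% to 16% in simulation, or 10% to 18% by formula, instead of 5%. These sizes rest on assumptions outside the article; equal dropout by one mechanism brings the bias to about zero.

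Two stronger readings are not supported. The bias need not favour counseling, because people who stop after improving would push it the other way. And the 8–10 session range is not a device for choosing completers afterwards: section 2.3 presents it as provisional, pending the results of Study 2.

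**What to change.** In section 3, state that the comparison of all participants as randomised is the sole basis for the Study 3 conclusion, and label the completer analysis supportive.

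In section 2.3.2, state that participants who stop counseling are still sent the online T1 and T2 questionnaires unless they refuse data collection, and that these observed scores, not carried-forward values, enter the as-randomised analysis. This second change does most of the work, because LOCF alone leaves much of the bias in place. It does not help for people who also decline the questionnaires; their scores remain missing.

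The cost is two wording changes, a few extra questionnaires, and a headline estimate that may be less favourable than the completer one. The sample size does not change.

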### 1.1. Bereavement and Grief Reactions

Grief is the natural response to losing a loved one. Most individuals adapt to their loss in natural ways. However, there exist substantial variations between individuals in terms of adjustments to loss [3]. In fact, various responses to loss tend to follow several distinct trajectories [4]. After the initial period of losing a loved one, some people could gradually adapt to the new life and move on with their love and memories of the deceased. For others, however, their process of adjusting to the grief is interfered. For a few people, negative mental and physical health consequences are extreme and persistent after bereavement. Individual factors such as maladaptive thoughts, dysfunctional behaviors, or inadequate emotion regulation can largely impede this process [5]. The sudden and unexpected death of a significant individual in one’s life is a highly intense stress event. It can trigger a series of grief reactions, including changes in emotion, cognition, behavior, and physiology [6].

With regard to emotional reactions, the bereaved may have feelings of depression, anxiety, anger, despair, loneliness, longing, and guilt; in terms of cognitive reactions, there may be rumination, self-blame, low self-evaluation, and meaninglessness. At the same time, the bereaved may show behavior reactions such as crying, nervousness, social withdrawal, and repeated search for the deceased. In addition, there may also arise some physiological problems, such as loss of appetite, insomnia, and fatigue [4,6,7,8,9,10]

For most of the bereaved, they can gradually accept the reality of loss and adapt to new life without the deceased under the influence of some factors, such as adequate social support, traditional funeral rituals, and meaning reconstruction [11]. However, studies have suggested that some bereaved people may develop intense and continuous symptoms in emotional, cognitive, behavioral, and physiological aspects, which may lead to the impairment of their mental or physical health and social functions [6,7,10,12].

The topic of grief and loss is a common issue for people all around the world [13]. The establishment of diagnostic criteria will facilitate the development of research and practice in grief field, and the diagnostic criteria applicable to clinical and practical applications will be beneficial to improve clinical utility [14].

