### 1.3. Grief Counseling and Grief Therapy

We often say “time will cure everything”. However, for individuals with prolonged grief disorder, they may experience a stronger grief response over time, without the help of professional grief counselors [32]. Moreover, the prolonged grief disorder does not only lead to emotional pain and impaired social function for the patients themselves, but also brings heavy stress and pain to other relatives.

Grief is a natural experience after loss, but for those bereaved who have difficulty adapting to grief, seeking help from psychotherapy is important [33]. Consequently, more research is needed to explore short-term, evidence-based, grief-focused, and effective psychological treatments.

The present grief treatments include: (a) meaning reconstruction [34], emphasizing that reconstruction of lost meaning is an important process of grief adapting; (b) complicated grief treatment (CGT) [5], focusing on the two directions of coping with loss and rebuilding a new life; (c) cognitive-behavioral therapy for complicated grief (CBT-CG) [35], helping individuals to integrate loss experiences into their autobiography through imaginal exposure, cognitive restructuring, and behavioral activation, while reducing negative self-evaluation, dysfunctional beliefs, and their avoidance behavior, and finally achieving the purpose of helping them better adapt to their life after loss.

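### In Study 3, carrying the last observation forward freezes dropouts at scores the protocol expects to change; with 20% dropout this can bias the treatment effect

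*Protocol article*

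**What the plan says.** Section 3 (Statistics Analyses) plans completer analyses and states that "intention-to-treat analyses (using the method of last observation carried forward) will be carried out". No other way of handling missing outcomes is mentioned, and neither analysis is named as primary. The sentence opens the section and is not tied to one study.

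For Study 3, section 2.3.2 bases the sample size on the "expected difference on the primary outcome variable (grief symptoms of the bereaved) between the different groups". It states that "we expect a medium Cohen effect size of 0.5 in the intervention group", with "conventional significance (α) and power (1−β) levels of 0.05 and 0.80, respectively" and "an expected dropout percentage of 20" per cent, and arrives at 80 per group. Assessments are at baseline before randomization (T0), post-counseling (T1) and three months later (T2). The outcomes are analyzed with a 2 × 3 repeated-measures MANOVA, followed by ANCOVA with the baseline score as covariate.

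On the course of grief, section 1.1 says "Most individuals adapt to their loss in natural ways". Section 1.3 says of people with prolonged grief disorder that "they may experience a stronger grief response over time". The Discussion again describes diverging trajectories after loss.

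**The concern.** Last observation carried forward is unbiased only if, on average, a participant's score would have stayed where it was last seen, or if the errors cancel between arms. The protocol's own description of grief contradicts the first condition, and nothing in the design secures the second.

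No assessment falls between T0 and T1. Anyone who leaves during counseling or the waiting period therefore has no score after randomization, and the baseline value stands in for both later outcomes. For that participant the analysis records neither a treatment effect nor natural change. At 20% dropout, up to 0.20 × 160 = 32 participants could be affected.

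Two things are at stake. The estimated effect depends on who leaves and when, not only on what counseling does. And because the only other analysis omits dropouts altogether and no primary is named, two analyses with different weaknesses could give different answers, with no rule for choosing between them.

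**Working it through.** **Inputs from the protocol:** effect 0.5 SD, α 0.05, power 0.80, dropout 20%, 80 per arm. Two-sided testing is stated in the Study 2 paragraph ("2-tailed) will be taken to indicate statistical significance") and is assumed here for Study 3.

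**Inputs the protocol does not give, so assumed:** the share of dropouts leaving before T1, the split of dropout between arms, the size of the natural fall in grief scores (c, in SD), and the correlation between baseline and outcome. Dropout is taken as unrelated to the outcome.

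**1. The plan's own figure.** A two-sample t-test with d = 0.5 and 80% power needs 64 per arm, and 64 / (1 − 0.20) = 80. The normal approximation gives 63, and 63 / 0.80 = 78.75, rounded up to 79. The stated 80 per group reproduces. It treats dropouts as lost and powers 64 completers per arm at an undiluted 0.5 SD (power 0.80).

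**2. Expected estimate at T1 when dropouts carry the baseline score.** With dropout p₁ (counseling) and p₀ (waitlist), all before T1, and true effect δ:

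estimate = (1 − p₁)(c + δ) − (1 − p₀)c

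| True effect δ | Dropout, counseling / waitlist | Natural fall c | Calculation | Estimate (SD) |
|---|---|---|---|---|
| 0.50 | 20% / 20% | any | 0.8 × 0.5 | 0.40 |
| 0.50 | 30% / 10% | 0.3 | 0.7 × 0.8 − 0.9 × 0.3 | 0.29 |
| 0.50 | 10% / 30% | 0.5 | 0.9 × 1.0 − 0.7 × 0.5 | 0.55 |
| 0 | 10% / 30% | 0.3 | 0.9 × 0.3 − 0.7 × 0.3 | 0.06 |
| 0 | 10% / 30% | 0.5 | 0.9 × 0.5 − 0.7 × 0.5 | 0.10 |

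The first row uses the protocol's dropout figure plus the assumption about timing and equal split. The others are illustrations.

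**3. Power with equal dropout, 80 analyzed per arm.** Unadjusted T1 comparison, no natural fall:

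- None of the 20% leave before T1: d = 0.50, power 0.88.
- Half leave before T1: d = 0.5 × (1 − 0.10) = 0.45, power 0.81.
- All leave before T1: d = 0.40, power 0.71. With a natural fall of 0.5 SD in both arms the extra spread lowers this to about 0.67.

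The planned ANCOVA with all dropouts before T1 (simulation, natural fall 0 to 0.5 SD) has power of about 0.83 to 0.88 at a baseline correlation of 0.5, 0.74 to 0.79 at 0.3, and 0.68 to 0.73 at 0.

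**4. Unequal dropout, correlation 0.5 (simulation).** With a true effect of 0.5 SD at T1 and T2, 30%/10% dropout and a 0.3 SD fall, carrying forward gives power of about 0.49 for the 2 × 3 group-by-time test and 0.58 for ANCOVA. The 2 × 3 test in completers has 0.82. With no true effect and 10%/30% dropout, the ANCOVA type I error is about 0.08 for a 0.3 SD fall and 0.11 for a 0.5 SD fall. The unadjusted test gives about 0.09 at 0.5 SD. Completer analyses stay near 0.05 here, because dropout was assumed unrelated to outcome.

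**The case against.** **Power.** A reader might infer that the method cannot deliver the planned 80% power. The documents do not support that. The figure of 160 follows from its inputs, and 0.71 requires every dropout to leave before T1 and a test that ignores baseline. The protocol gives no timing for dropout, and it plans an ANCOVA that stays above 0.80 at a correlation of 0.5 when dropout is equal. This objection stands: power can fall, but a shortfall is not shown.

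**Unequal dropout.** The protocol gives a single overall 20% and says nothing on the split, so a heavy imbalance is an assumption. With equal dropout the type I error stays near 0.05. With 15%/25% and a 0.3 SD fall the bias is only 0.03 SD and the type I error about 0.06. This stands as a limit on size. It does not remove the dilution that arises when dropout before T1 is equal.

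**All three studies.** The sentence is general, so a reader might apply it to Studies 1 and 2 as well. But Study 1 is a single-group training evaluation and Study 2 an observational survey; neither has randomized arms or a treatment effect. Any figure for distortion in Study 2 would need a stability and a dropout rate that the protocol does not give. The fair request there is to narrow the wording.

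**Completers.** They are analyzed as well, and theirs is the comparison that the sample size powers, so disagreement between the two would be visible. That is true. But a completer analysis leaves out randomized participants and is biased if leaving depends on outcome in ways the model does not capture. Without a named primary, visible disagreement is not resolved.

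**Detail left to an analysis plan.** Much may be left to one, but here the article states the method, and the stated method is the problem.

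**Conclusion.** The point holds for Study 3. The stated method for the intention-to-treat analysis assumes stable scores, the protocol expects scores to move, and one participant in five is expected to drop out.

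If all dropouts leave before T1, equally in both arms, a true 0.50 SD is estimated as 0.40 SD, a dilution of one fifth whatever the natural change. Dropout after T1 dilutes less. If dropout is unequal and grief eases on its own, the bias can go either way: 0.29 SD for a true 0.50 SD in one assumed scenario, and 0.06 to 0.10 SD of false benefit with ANCOVA type I error of about 0.08 to 0.11 in the reverse one. Baseline adjustment does not remove that error.

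The unequal-dropout results rest on assumed splits, natural falls and a correlation of 0.5, and show what could happen, not what is expected. There is no finding against the sample size, and none on treatment effects in Studies 1 and 2.

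**What to change.** Change one paragraph of section 3:

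- Limit the intention-to-treat sentence to Study 3.
- Replace last observation carried forward with a likelihood-based mixed model for repeated measures and name it as the primary analysis. Include all randomized participants with any observed T1 or T2 score, in the arm to which they were assigned, with baseline score as covariate and group, time and group-by-time as effects.
- Keep the completer analysis as supportive.
- Add one sensitivity analysis for data not missing at random. It should also cover participants with no score after baseline, who contribute no outcome to the mixed model.

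The model is available in the SPSS package already named (MIXED). No extra data or participants are needed, and the total of 160 does not change. The small downside is reliance on a missing-at-random assumption, which the data cannot confirm; the sensitivity analysis shows how far the conclusion depends on it.

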##### Demographic and Loss-Related Information

Demographic information includes age, sex, education level, marital status and religious belief. Loss-related information includes the relationship with the deceased, time since the loss, and the cause of death.

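### Study 3 tests baseline differences for significance, which cannot show balance after randomisation, and tests time since loss without adjusting for it; a small, nearly free improvement

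*Protocol article*

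**What the plan says.** Section 2.3.2 assigns 160 bereaved participants at random to grief counseling or a waitlist. Section 3 then sets out three steps for Study 3.

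- Baseline comparison: "Chi-square tests and ANOVAs will be conducted on baseline scores to rule out significant differences between groups". The variables named are demographic, loss-related and outcome variables.
- Main test: a repeated-measures MANOVA with two groups and three time points, baseline being one of the three. No covariate is named.
- Follow-up test: ANCOVAs "using baseline scores of the outcome variables as covariates". No other covariate is named.

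Time since loss appears in the Study 2 measures: "Loss-related information includes the relationship with the deceased, time since the loss, and the cause of death". Its collection in Study 3 is implied, because loss-related variables are to be tested there, but it is not stated outright. Section 2.3.2 refers the Study 3 measures back to Study 3 itself, and Table 2 has a row for socio-demographic information but none for loss-related information. Eligibility (sections 2.2.1 and 2.3.1) requires the loss to fall within the COVID-19 period and gives no further window.

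**The concern.** When allocation is random, any baseline difference between arms is due to chance. A significance test of that difference therefore asks a question whose answer is already known. It can mislead in two ways. A significant result may cast doubt on a sound randomisation. A non-significant result may be taken as proof of balance when an imbalance in a prognostic variable remains.

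Whether an imbalance matters depends on its size and on how strongly the variable predicts the outcome, not on its p-value. The useful response is to name prognostic covariates beforehand and adjust for them whatever the data show. Time since loss is a plausible candidate: sections 1.1 and 4 describe grief as changing after the initial period, and recently and less recently bereaved people may enter together. As written, the plan tests this variable but adjusts for it in no Study 3 model. At stake are some precision and protection against a chance imbalance.

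**Working it through.** **1. The plan's sample size.** Inputs from section 2.3.2: "the conventional significance (α) and power (1−β) levels of 0.05 and 0.80, respectively"; "we expect a medium Cohen effect size of 0.5 in the intervention group"; "an expected dropout percentage of 20" per cent. Two-sided testing is taken from section 3 ("A *p*-value < 0.05 (2-tailed) will be taken to indicate statistical significance"). That sentence sits in the Study 2 paragraph, so its use for Study 3 is an assumption.

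- Normal approximation: n = 2(1.96 + 0.84)² / 0.5² = 63 per arm; 63 / 0.8 = 79.
- t-test version: 64 per arm; 64 / 0.8 = 80, or 160 in total.

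Both agree with "we will need almost 80 participants for each group". The steps below use 80 per arm at baseline and 64 completers per arm.

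**2. False alarms.** Variables within the stated scope: 5 demographic, 3 loss-related and about 9 scale scores (PG-13, ITG, PCL-5, PTGI, DASS-21, TBQ, GRAQ, WSAS, SSI), making 17. Therapy expectations is none of the three kinds and is left out.

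- 17 independent tests: 1 − 0.95^17 = 58%.
- The 8 demographic and loss-related variables alone: 1 − 0.95^8 = 34%.

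The scales measure related distress, so 58% is an upper figure for 17 tests.

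**3. Imbalance that passes.** The standard error of a standardised baseline difference at 80 per arm is sqrt(2/80) = 0.158. The significance threshold is 1.96 × 0.158 = 0.31 SD. An observed gap of 0.30 SD gives 0.30 / 0.158 = 1.90, p about 0.06, and passes. The same calculation gives how often chance produces a gap at least that large in either direction: about 6% of randomisations.

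**4. Effect of such a gap on the estimate.** Shift = imbalance × correlation of time since loss with the outcome. The article gives no correlation; 0.1 to 0.4 is assumed.

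| Assumed r | Shift for a 0.3 SD gap | Share of planned 0.5 |
|---|---|---|
| 0.1 | 0.03 SD | 6% |
| 0.2 | 0.06 SD | 12% |
| 0.3 | 0.09 SD | 18% |
| 0.4 | 0.12 SD | 24% |

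This applies to an estimate not adjusted for time since loss. If r is the correlation remaining after baseline adjustment, it acts on the residual SD. With an assumed baseline-outcome correlation of 0.5, that SD is sqrt(1 − 0.25) = 0.866, and the range becomes about 0.03 to 0.10 SD.

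**5. Precision gained by adjusting.** Residual SD = sqrt((1 − r_base²)(1 − r²)), with 64 completers per arm, d = 0.5 and assumed r_base = 0.5. Power without time since loss is 90.4%.

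| Assumed partial r | Residual variance removed | Power with time since loss |
|---|---|---|
| 0.1 | 1% | 90.7% |
| 0.2 | 4% | 91.5% |
| 0.3 | 9% | 92.8% |
| 0.4 | 16% | 94.6% |

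With no baseline adjustment, the same steps move power from 80.7% to 81.1%, 82.3%, 84.3% and 87.0%.

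**The case against.** The strongest reply is that the plan already adjusts for the most useful covariate. The ANCOVA uses the baseline outcome scores, which may carry part of the information in time since loss. That stands, and it rules out reading the plan as using tests in place of adjustment. The gap concerns time since loss only.

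It can also be said that the choice of covariate is a matter of judgement. Section 1.5 names unexpected death, social isolation and multiple losses as hindering factors, and the Study 2 control list omits time since loss. Section 1.1 describes differing trajectories, and section 1.3 says grief may intensify over time in prolonged grief disorder, so a simple linear relation is uncertain. Further covariates may also be fixed in an analysis plan that is not shown. All of this limits the size of the gain. None of it defends the baseline tests, whose purpose the article states outright.

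A reader might infer three stronger things that the article does not support.

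- That the test results decide which covariates enter the models. Section 3 does not say so; later covariate choices prompted by them are a risk, not a plan.
- That time since loss is unlimited. The loss must fall in the COVID-19 period. The introduction places the first identification in December 2019 and gives deaths as of 18 August 2021, so the range was about 20 months at that date. A narrower range tends to weaken the correlation.
- That the treatment comparison is biased. Randomisation keeps it valid on average; the issue is efficiency and the estimate given a particular chance imbalance.

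**Conclusion.** The point holds as a minor one. The baseline tests cannot serve their stated purpose, and that conclusion needs no assumed correlation: up to about 58% false alarms over 17 tests (34% over 8), and observed gaps of up to about 0.31 SD passing unnoticed at 80 per arm. Removing the tests would not by itself change any treatment estimate.

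The benefit of adjusting for time since loss is real in direction but uncertain in size. It is negligible at a partial correlation of 0.1 and moderate at 0.4. The larger shifts in the estimate need both a correlation near the top of the assumed range and an imbalance that few randomisations produce. The sample size itself reproduces and is not in question.

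**What to change.** - Replace the baseline tests in section 3 with a table of baseline characteristics by arm, without p-values.
- State that each Study 3 ANCOVA includes the outcome's baseline score and time since loss, whatever balance is observed.
- In the MANOVA, baseline is already one of the repeated responses and should not also be a covariate. If any covariate is used there, add time since loss only.
- Correct the self-reference in section 2.3.2 and confirm, there or in Table 2, that time since loss is collected in Study 3.

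The cost is a few sentences and one model term. No extra participants are needed and, if collection is confirmed, no extra data. The downside is a weak assumption about the form of the covariate's effect, for example linear or grouped, which should be fixed beforehand.
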